### Intervention

The intervention (figure 1) consists of the execution of a redesigned care pathway for stroke patients admitted to the Maastricht University Medical Centre. Every patient with a suspected stroke will be analysed in the emergency ward. In case of a stroke, the patient will be admitted to the stroke unit of the hospital, where, if indicated, thrombolysis will be followed by further diagnosis and treatment. The new aspect of the critical care pathway consists of a strict discharge regime in the neurology department of the hospital. All necessary testing and treatment in the hospital can be performed within 5 admission days, after which patients may be discharged if medically stable. The underlying assumption for the design is that hospitals are specialized in acute care and treatment and do not provide optimal rehabilitation facilities. From a cost effectiveness point of view as well, it seems more appropriate to provide rehabilitation in a centre specialised for this purpose.

**Figure 1 F1:**
[figure not shown]
**Flowchart of the study**.

In the redesigned care pathway, after 5 days all stroke patients are discharged to a nursing home with a specialised assessment unit, resulting in a tailored rehabilitation programme. Only patients who can be discharged directly to their home within five days, or patients with complications requiring prolonged hospital care, will not be referred to the specialised nursing home unit. The nursing home physician examines each patient immediately on arrival in the nursing home and initiates the assessment program. In this program a multidisciplinary team, consisting of a psychologist, physiotherapist, occupational therapist, speech therapist, and trained nurses, examine the patient by means of a structured assessment protocol. Following assessment, the team will meet within five days of the patient's admission to make recommendations for the best rehabilitation program. Their advice will be based on admission and discharge criteria formulated by the various care providers participating in the stroke service. A structured possibility for the nursing home physician to consult a rehabilitation physician, if needed, is arranged. After the multidisciplinary meeting the patient and his family will be informed about the proposed rehabilitation track and after their approval this track can be started.

There are three options for rehabilitation after the assessment.

1. Rehabilitation at home with outpatient care provided by therapists from primary healthcare or day care rehabilitation in a hospital or nursing home

2. Inpatient rehabilitation in a nursing home

3. Inpatient rehabilitation in a rehabilitation centre

### Usual care

The redesigned stroke service provided by the Stroke Service Maastricht Heuvelland, the intervention region, will be compared to "care as usual" provided by the stroke service in the Eindhoven area.

In the Stroke Service Eindhoven stroke patients are admitted to the stroke unit of the Catharina hospital in Eindhoven, where diagnostic tests, treatment and observation take place. During the patients' stay in the hospital, an assessment is performed in order to determine the best suitable rehabilitation facility for the stable patient. A physiotherapist, an occupational therapist and trained nurses carry out the assessment; if necessary they are supported by a speech therapist or a psychologist.

On the basis of admission and discharge criteria formulated by the various care providers who participate in the Stroke Service Eindhoven, the patient can be discharged to home, to a rehabilitation centre or to one of four nursing homes participating in the stroke service. The mean duration of the hospital stay in Eindhoven is 10 days. Consequently, the main differences in care arrangements between the experiment and the control region are the early hospital discharge and the structured assessment in the nursing home.

### Effect evaluation

The primary outcome measures of the effect evaluation are quality of life and activities of daily life (ADL). Quality of life is measured by means of the Stroke Adapted Sickness Impact Profile 30 (SA-SIP 30)[12] and ADL by means of the Barthel index (BI)[13,14].

Secondary outcome measures are: instrumental activities of daily living (IADL) measured by means of the Frenchay Activity Index (FAI)[15], handicap measured by means of the Modified Rankin Scale (MRS)[16]. Cognitive functioning is measured by means of Mini Mental State Examination (MMSE)[17], Apraxia Test (AT)[18] and Star Cancellation Test (SCT)[19]. Anxiety and depression are measured by the Hospital Anxiety and Depression Scale (HADS)[20] and the patients' satisfaction with stroke care is measured by means of the Satisfaction with Stroke Care Questionnaire (SASQ-19)[21]. The strain on caregivers is measured by the Caregivers Strain Index (CSI)[22].

Other secondary outcome measures are medical complications occurring within 3 months after stroke. The following diagnoses are regarded as medical complications: a new stroke, epileptic seizures, pneumonia, urinary tract infections, fractures, bedsores, myocardial infarct, heart failure and atrial fibrillation. The data on medical complications will be collected from the patients' files.

Besides the primary and secondary outcome measures we assess some background variables which are considered to be predictors, confounders or effect modifiers. The following personal characteristics are assessed: age, sex, socio-economic status, risk factors, co-morbidity, stroke location and stroke severity measured by the National Institute of Health Stroke Scale (NIHSS)[23]. All background variables are measured at baseline.

### Economic evaluation

The economic evaluation compares costs and outcomes of stroke care given in the Stroke Service Maastricht Heuvelland to care as usual provided by the Stroke Service Eindhoven. The economic evaluation will involve a combination of a cost-effectiveness analysis (CEA) and a cost-utility analysis (CUA). In a CEA effects are presented in clinical outcomes.

The primary outcome measure of the cost-effectiveness analysis will be the SASIP-30. Within the cost-utility analysis, outcomes will be measured by means of the standard Dutch version of the EuroQol (EQ-5 D)[24]. This is a self-administered questionnaire, which will be completed together with the cost questionnaire at 12 weeks and 26 weeks.

Both generic quality of life, as well as utilities, will be derived by means of the EQ-5 D. The EQ-5D is chosen because it is a widely used quality of life instrument. The EQ-5D contains 5 dimensions of health-related quality of life; mobility, self-care, daily activities, pain/discomfort and anxiety/depression. Each can be rated at three levels: no problems, some problems and major problems. The 5 dimensions can be added to comprise an overall health state. This health state will be translated into a number, a utility. Utility values can be calculated for these health states, using preferences elicited from a general population, the so-called Dolan algorithm[25]. The utility values derived from the Dolan algorithm will be used to compute Quality Adjusted Life Years (QALYs). The Dolan algorithm has been established using a general population from the UK. Recently a Dutch algorithm has become available, and this will be used in the sensitivity analysis[26]. The utilities at the two time points are used to compute a Quality Adjusted Life Years (QALY) score by means of the area under the curve method. Furthermore, the EQ-5D consists of a visual analogue scale (VAS) ranging from zero (worst imaginable health state) to 100 (best imaginable health state). The reliability and validity of the EQ-5D has been established[27]. The primary outcome measure for the cost-utility analysis will be Quality Adjusted Life Years (QALYs), based on the EuroQol utility scores[24,27]. In the CUA, the incremental cost-effectiveness ratio (ICER) will be expressed as the incremental costs per QALY. This economic evaluation will be performed from a societal perspective, which implies that all relevant costs and outcomes will be taken into account.

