**Methods/design:**

The design involves a non-randomised comparative trial for two groups. Participants are followed for 6 months from the time of stroke. The intervention consists of a redesigned care pathway for stroke patients. In this care pathway, patients are discharged from hospital to a nursing home within 5 days, in comparison with 12 days in the usual situation. In the nursing home a structured assessment takes place, aimed at planning adequate rehabilitation. People in the control group receive the usual care. The main outcome measures of the effect evaluation are quality of life and daily functioning. In addition, an economic evaluation will be performed from a societal perspective. A process evaluation will be carried out to evaluate the feasibility of the intervention as well as the experiences and opinions of patients and professionals.

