### Instruments

The instruments used in this study are shown in Table 1

**Table 1 T1:** Overview of instruments per time point

	Time after stroke			
Instrument	T0	T1	T2	T3
	< 1 week	4 Weeks	12 Weeks	26 Weeks
SA-SIP30			X	X
Barthel index	X	X	X	X
Frenchay Activities Index	X			X
Modified Rankin Scale	X	X	X	X
Mini Mental State Examination	X			X
Apraxia Test	X			X
Star Cancellation Test	X			X
Hospital Anxiety and Depression scale		X		X
SASC-19	After every discharge			
Caregivers Strain Index				X
EQ-5D			X	X
Cost Questionnaire			X	X

Instruments used for the screening process, the clinical outcome assessment and the economic evaluation. In Table 1 an overview of all assessments per time point is shown.

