### Effect analysis

For the analyses we will use SPSS statistical software and Excel (for the Bootstraps). Missing data on the item level will be handled using SPSS missing value analysis. If considerable data are missing related to specific instruments, imputation will be considered.

A baseline analysis will be performed to examine the comparability of groups at baseline for both costs and outcomes. If necessary, methods will be applied to correct for differences in baseline[30]. A Kolmogorov-Smirnov test will be performed to investigate whether the data are normally distributed. If the data are distributed normally, our primary analysis will start with a t-test. If data are skewed, the primary analysis will be based on a non-parametric test for assessing two independent samples, i.e. a Mann-Whitney U test.

As it is known that in non-randomised comparative studies, variations in case mix between centres can influence the interpretation of outcome data[31], we would like to explore this in further analysis. Therefore, for each of the data sets collected at all measurement points, differences in outcome variable between the 2 regions will be tested using multiple MANCOVAs, entering various indicators of case mix as co-variates, i.e. age, gender, stroke severity. In addition, information on possible confounding factors and effect modifiers will be collected and analysed.

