Despite the usual skewness in the distribution of costs, arithmetic means are generally considered the most appropriate measure to describe cost data[36,37]. Therefore, arithmetic means (and standard deviations) will be presented. In case cost data are skewed, non-parametric bootstrapping will be used to test for statistical differences in costs between the intervention and control group. Non-parametric bootstrapping is a method based on random sampling with replacement based on the individual data of the participants[38]. The bootstrap replication will be used to calculate 95% confidence intervals around the costs (95% CI), based on the 2.5 th and 97.5 th percentiles. If cost data are distributed normally, t-tests will be used.

The incremental cost effectiveness ratio (ICER) will be determined on the basis of incremental costs and effects of the intervention compared to care as usual. The cost effectiveness ratio will be stated in terms of costs per outcome rate; the cost utility ratio will focus on the net cost per QALY gained.

The ICER will be calculated as follows. ICER = (Ci-Cc)/(Ei-Ec), where Ci represents the total costs of the intervention group at the 26-weeks follow-up, Cc the total costs of the care as usual group at the 26-weeks follow-up, Ei the effects at the 6-month follow-up for the intervention group and Ec the effect at the 26-weeks follow-up for the care as usual group. The robustness of the ICER will be checked by non-parametric bootstrapping (1000 times). Bootstrap simulations will also be conducted in order to quantify the uncertainty around the ICER, yielding information about the joint distribution of cost and effect differences. The bootstrapped cost-effectiveness ratio will be plotted subsequently in a cost-effectiveness plane, in which the vertical line reflects the difference in costs and the horizontal line reflects the difference in effectiveness.

The choice of treatment depends on the maximum amount of money that society is prepared to pay for a gain in effectiveness, which is called the ceiling ratio. Therefore, the bootstrapped ICERs will also be depicted in a cost effectiveness acceptability curve showing the probability that the intervention care is cost effective using a range of ceiling ratios.

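### No utility is measured before week 12, so the QALYs leave the first 12 weeks after stroke unobserved while the ICER uses total costs at 26 weeks

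*Protocol article*

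**What the plan says.** The protocol article's Economic evaluation section makes QALYs the primary outcome of the cost-utility analysis. It describes the EQ-5D as a self-administered questionnaire "which will be completed together with the cost questionnaire at 12 weeks and 26 weeks". Table 1 under Instruments ("Overview of instruments per time point") agrees: the EQ-5D is marked at T2 (12 weeks) and T3 (26 weeks), not at T0 (under 1 week) or T1 (4 weeks). QALYs are then derived as follows: "The utilities at the two time points are used to compute a Quality Adjusted Life Years (QALY) score", using the area under the curve. No starting utility is measured, and none is assumed.

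The horizon is half a year: "Participants are followed for 6 months from the time of stroke". In the ICER formula under Economic analysis, "Ci represents the total costs of the intervention group at the 26-weeks follow-up", and the control group's costs are defined in the same way. Costs include those of the intervention and of health care generally.

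Under Effect analysis, "A baseline analysis will be performed to examine the comparability of groups at baseline for both costs and outcomes", with correction for differences if necessary.

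**The concern.** The Usual care section names two main differences between the regions: early hospital discharge and the structured assessment in the nursing home. Both fall in roughly the first two weeks. The abstract contrasts discharge within 5 days with 12 days usually, and the Intervention section has the team meet within five days of nursing-home admission. The cost side captures what the shorter hospital stay saves. The utility side has no measurement until week 12, so it cannot show what patients gained or lost in quality of life while that saving was made.

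This matters because the Sample Size section gives the primary goal as lower cost without loss of quality of life. A temporary loss after early transfer is one of the things a QALY should be able to reveal. The Economic evaluation section also promises that its societal perspective takes in every relevant cost and outcome.

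A second consequence is that QALYs cannot be adjusted for baseline utility, in a two-region comparison whose Discussion concedes possible bias from non-randomisation.

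**Working it through.** The protocol states no expected QALY difference, so there is no figure of its own to reproduce. The check below is area-under-the-curve arithmetic.

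**Inputs**
- EQ-5D at weeks 12 and 26 only (Economic evaluation; Table 1).
- Follow-up of 26 weeks from stroke (abstract; Table 1).
- Utility difference of 0.11, taken from the Sample Size section, where it comes from an earlier stroke study. It is used here only to show scale.
- The time courses of the gap below are assumptions.

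**Formula.** QALY difference = sum over intervals of (mean of the utility gaps at the two ends) × (interval length in weeks / 52).

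**Span, read literally**
- Covered: 26 − 12 = 14 weeks; 14/26 = 53.8%; 14/52 = 0.269 year.
- Not covered: 12 weeks; 12/26 = 46.2%; 12/52 = 0.231 year.

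**Constant gap of 0.11**
- Weeks 12 to 26: 0.11 × 14/52 = 0.0296 QALY.
- Weeks 0 to 26: 0.11 × 26/52 = 0.0550 QALY.
- Left out: 0.11 × 12/52 = 0.0254 QALY.
- Ratio: 26/14 = 1.86.

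**Gap at stroke that falls linearly to zero by week 12**
- Under the plan: 0, because the gap is zero at both measured points.
- Over 26 weeks, start +0.11: (0.11 + 0)/2 × 12/52 = +0.0127.
- Start −0.11: −0.0127.
- Start +0.05: (0.05 + 0)/2 × 12/52 = +0.0058.

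**Week-12 utility carried back to stroke** (not stated in the article)
- Constant gap of 0.11: 0.11 × 26/52 = 0.0550, so the factor 1.86 disappears.
- Fading gap: still 0, because the week-12 gap of zero is carried back. The early difference remains unseen.

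**With the EQ-5D added at week 4 only**
- Observed span: 26 − 4 = 22 of 26 weeks (84.6%).
- Fading gap starting at 0.11: the gap at week 4 is 0.11 × 8/12 = 0.0733, and the area over weeks 4 to 12 is 0.0733/2 × 8/52 = 0.0056, out of 0.0127 in total. The 4-week visit helps, but it does not recover all of an early effect.

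**The case against.** Several points on the other side are sound and limit what can be claimed.

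- **The window is inferred.** The article gives neither integration limits nor a rule for weeks 0 to 12, and its ICER definition places effects only at the 6-month follow-up. A condensed article may leave such detail to a fuller document. A reader might infer that cost per QALY will be inflated 1.86-fold. The documents do not support that as a fact: it needs the literal 14-week reading and a constant gap, and it vanishes if week 12 is carried back.
- **The cost horizon is inferred.** The recall period of the cost questionnaire is not written out. Coverage of weeks 0 to 26 is still a strong inference, since total costs at 26 weeks without the early weeks would omit the very hospital stay the redesign shortens.
- **Direction is unknown.** Early discharge could raise or lower early utility. If costs fall and the QALY difference is near zero, the ratio is unstable and talk of inflation has no clear meaning.
- **Baseline correction is not ruled out.** A reader might infer that QALYs cannot be corrected at all. NIHSS, Barthel and Rankin are measured at baseline and can serve as covariates. Only adjustment for baseline EQ-5D itself is impossible.
- **Early harm is not invisible to the study.** Barthel and Rankin at T0 and T1, the HADS at T1 and complications within 3 months cover this period, and lasting effects still show in the EQ-5D from week 12. The gap concerns the cost-utility analysis. The SA-SIP30 and Barthel effect evaluation is unaffected.

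What survives is the measurement gap. Measurement times and method are stated consistently in text and table, and no choice of integration limits supplies an early group difference that nobody measured.

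**Conclusion.** The point holds in this form. The planned QALYs contain no observed utility from weeks 0 to 12, the period in which the two pathways differ most directly, while the ICER sets them against costs that very probably run over all 26 weeks.

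On the literal reading, 54% of follow-up is covered. The illustrative shortfall is 0.0254 QALY for a constant gap of 0.11, and an early gap of either sign that fades by week 12 is missed completely. These sizes rest on the assumed time courses and on borrowing 0.11 from the sample-size section; they do not predict this trial's result. The direction of the bias cannot be stated.

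The loss of baseline EQ-5D adjustment is real but partial, because other baseline severity and function measures remain available. QALYs are the primary outcome of the cost-utility analysis and serve one of the main research questions, so the gap should be closed or openly handled before a cost per QALY is reported.

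**What to change.** **If patients can still be assessed.** Add the EQ-5D to the existing T1 (4-week) assessment and, where patients can self-report, to T0. Compute QALYs from stroke to week 26, adjusting for baseline utility where available and for baseline NIHSS, Barthel and Rankin. State the integration limits and the recall period of the cost questionnaire, so that costs and effects visibly share one horizon.

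The cost is a short extra questionnaire at assessments that already take place. The main drawback is non-response at T0, which is likely to depend on severity. T0 falls within the first week and discharge can occur within 5 days, so T0 may not precede discharge for everyone. T1 alone extends observed coverage to weeks 4 to 26 but gives no baseline value and leaves the first four weeks to assumption.

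**If patients are already enrolled without it.** Estimate utility in weeks 0 to 12 from the T0 and T1 Barthel and Rankin scores, using their relation to the EQ-5D at T2 and T3, where all three are collected. This assumes that the later relation also holds early after stroke, so it needs a sensitivity analysis over the early-utility assumption. It costs analysis time only.

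**If neither is done.** Report the result as 12-26 week QALYs and do not divide 26-week costs by it.

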### Process evaluation

The process evaluation consists of two parts. The first part of the process evaluation consists of assessing whether care after the redesign was performed in the time planned. For this part of the process evaluation, the patients' files will be screened for protocol violations related to the discharge time from hospital, according to protocol, and the duration of assessment in the nursing home. If possible the reasons for these protocol violations will be collected from the patients' files as well.

The second part assesses how patients, their personal caregivers and professionals experience care after the redesign. Data will be collected from 20 patients and from their personal caregivers. Data will also be collected from 20 professionals working in the redesigned care system. The data will be collected by means of semi-structured in-depth interviews. The patients and professionals will be selected by means of purposeful sampling, to ensure that the interviewees are heterogeneous on relevant determinants such as age, severity of disease, level of functioning, housing situation (living alone, stairs, etc.). The patients will be interviewed at home or in the institution were they are being cared for.

To ensure the open character of the interviews they will be held by a person who is not related to the direct project group. All interviews will be audiotaped and transcribed verbatim.

### Instruments

The instruments used in this study are shown in Table 1

**Table 1 T1:** Overview of instruments per time point

	Time after stroke			
Instrument	T0	T1	T2	T3
	< 1 week	4 Weeks	12 Weeks	26 Weeks
SA-SIP30			X	X
Barthel index	X	X	X	X
Frenchay Activities Index	X			X
Modified Rankin Scale	X	X	X	X
Mini Mental State Examination	X			X
Apraxia Test	X			X
Star Cancellation Test	X			X
Hospital Anxiety and Depression scale		X		X
SASC-19	After every discharge			
Caregivers Strain Index				X
EQ-5D			X	X
Cost Questionnaire			X	X

Instruments used for the screening process, the clinical outcome assessment and the economic evaluation. In Table 1 an overview of all assessments per time point is shown.

